### Secondary outcomes

The proportions of participants with confirmed progression at 36 months on the composite (multicomponent) disability progression outcome (EDSS, T25FW or 9HPT), and proportions with confirmed progression on the individual outcomes making this composite, will be compared between arms using logistic regression adjusting for the minimisation variables as fixed effects. Proportions with progression on mRS at 36 months will also be compared using logistic regression, adjusting for the minimisation variables. ORs and 95% CIs will be presented along with the p value for a Wald test for the difference between treatment groups.

Baseline to 36 months change in continuous clinician and patient-reported outcomes will be compared between groups using linear mixed models for repeated measures. For each outcome, the difference in mean of the outcome at 36 months will be reported alongside 95% CIs and the two-sided p value. Analysis of MSIS-29v2, MSWS-12v2, MSFIS-21 and CFQ will use data recorded at all available visits. Analysis of MSFC, T25FW, 9HPT, SLCVA, CVLT-II, BVMT-R and SDMT will use data recorded at baseline and 36 months (due to COVID-19 as described below). The dependent variable will be the outcome at each time point. Treatment group will be included as predictor, with treatment by visit interaction, but at baseline the treatment effects will be constrained to be zero, which is essentially equivalent to adjusting for baseline using analysis of covariance (ANCOVA).^51^ An unstructured covariance matrix for the residuals will be used to allow for correlation between repeated measures on an individual. The minimisation variables, and their interactions with visit, will be included as fixed effects. If parametric assumptions for the linear regression model are substantially violated, bias-corrected and accelerated bootstrap confidence intervals will be used for inference.

The relapse rate up to 36 months will be compared between groups using negative binomial regression adjusting for the minimisation variables as fixed effects. Numbers of relapses by grade, adverse events, serious adverse events and notifiable adverse events will be tabulated by treatment group.

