## Methods and analysis

### Trial objective

Following the promising results of the MS-STAT phase 2 trial,^12^ the MS-STAT2 trial has been designed to determine whether simvastatin can slow the time to confirmed disability progression (CDP), based on the current regulatory standard of confirmed EDSS progression.^40^ The primary objective is to compare the effect of daily use simvastatin (80 mg) versus placebo on disability progression at 6 monthly intervals in patients with SPMS, based on change in EDSS score compared with baseline.

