#### Secondary outcomes

Clinician-reported secondary outcomes will include Timed 25 Foot Walk (T25FW); 9 Hole Peg Test (9HPT); Single Digit Modalities Test (SDMT); Sloan Low Contrast Visual Acuity (SLCVA); Relapse assessment; modified Rankin Scale (mRS) and Brief International Cognitive Assessment For Multiple Sclerosis comprising SDMT, California Verbal Learning Test-II (CVLT-II) and Brief Visuospatial Memory Test-Revised (BVMT-R).

Patient-reported outcomes will include MSIS-29v2; Multiple Sclerosis Walking Scale-12 v2 (MSWS-12v2); Modified Fatigue Impact Scale - 21 (MFIS-21); Chalder Fatigue Questionnaire (CFQ).

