### Trial schedule

Online supplemental table 1 presents the trial schedule of assessments. Following baseline/randomisation, where a full set of clinical assessments and patient-reported questionnaires will be completed, participants will attend the clinic for safety monitoring and dose escalation at 1 month. At 3 months, participants have a telephone check-up (with safety bloods arranged locally), and then will have further assessment visits at 6-monthly intervals from 6 months postrandomisation onward. Where participants are unable to attend 6-monthly follow-ups (such as due to COVID-19-related issues or participant logistics), a telephone-EDSS assessment will be undertaken,^46^ together with remotely collected patient-reported outcomes and locally performed safety bloods.

In terms of clinician-reported outcomes, the EDSS, 9HPT and T25FW will be performed 6 monthly; the SDMT, SLCVA and mRS annually; and CVLT-II and BVMT-R at baseline and the 36-month visits only. For patient-reported outcomes, the EQ-5D-5L and CSRI will be completed 6 monthly; with the CFQ, MFIS-21, MSIS-29v2 and MSWS-12v2 completed annually.

Participants will be evaluated at the 36-month time point visit to determine whether they have experienced EDSS CDP. Those participants yet to have CDP will be asked to consent to continued follow-up into the extension phase, at sites which agree to take part in the extension, as outlined in the ‘Intervention’ section.

At the lead site (University College London Hospitals Trust) only, additional subsidies will be conducted to investigate MRI, biomarker and optical coherence tomography outcomes.

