### Power and sample size

In order to have 90% power to demonstrate a 30% relative reduction in disability progression for simvastatin versus placebo, at the conventional 5% significance level, the trial will require a total of 330 progression events. This will be achieved by recruiting 1050 participants with 525 enrolled on each treatment arm. Individual participant trial duration will be a minimum of 36 months (core) and up to a further 18 months (extension) if there is no confirmed progression event by 36 months. This assumes that the placebo progression rate will be 40% by 36 months and 49% by 54 months^47^,^50^ and allows for 20% loss to follow-up by 36 months and 32% by 54 months (among those who are eligible for the extension). This is equivalent to a progression rate of 8% per 6 months among those who have yet to experience progression.

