### Analysis plan

A detailed statistical analysis plan has been written and signed off. All statistical tests will use a two-sided p value of 0.05 unless otherwise specified. Statistical analysis will be performed by using Stata v17.0 (StataCorp).

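### The modified Rankin Scale is analysed only as progression yes/no at month 36, with no full-scale analysis described; the test is valid but probably less precise than the data allow

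*Protocol article*

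**What the plan says.** The Outcomes section lists the scale among the clinician-reported secondary outcomes: "Relapse assessment; modified Rankin Scale (mRS) and Brief International Cognitive Assessment For Multiple Sclerosis". Trial schedule has a full set of clinical assessments at baseline and then "the SDMT, SLCVA and mRS annually".

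The analysis is fixed in Analyses, Secondary outcomes: "Proportions with progression on mRS at 36 months will also be compared using logistic regression, adjusting for the minimisation variables". The effect measure and test follow: "ORs and 95% CIs will be presented along with the p value for a Wald test for the difference between treatment groups". The minimisation variables (Treatment allocation) are sex, age group, baseline EDSS in two bands, use of newly licensed DMTs, and site. Baseline mRS is not among them.

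The article gives a reason for a progression endpoint in two other places. Trial objective bases the primary outcome on EDSS, "based on the current regulatory standard of confirmed EDSS progression". The Discussion explains a move to binary classification by missing face-to-face data during COVID-19 and names six tests; the mRS is not one of them.

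**The concern.** The mRS is an ordered scale. Cutting it to progressed or not progressed drops two kinds of information: how far a participant worsened, and whether a participant who did not worsen was stable or improved. The timed walk and peg test also have a progression endpoint, but the same section keeps a mixed model of their full measurements. The mRS has no such companion analysis.

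What is at stake is the precision of one secondary comparison. If simvastatin shifts global disability modestly, the binary comparison may be less likely to show it. Because baseline mRS is not in the model, the starting grade is represented only indirectly, through the two EDSS bands.

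**Working it through.** **1. The plan's own figure.** Power and sample size states: "In order to have 90% power to demonstrate a 30% relative reduction in disability progression for simvastatin versus placebo", with 330 events. Schoenfeld's formula gives 4 × (1.960 + 1.282)² / (ln 0.7)² = 42.03 / 0.1272 = 330.4 events, and 330 events give 89.97% power. So the 30% reduction behaves as a hazard ratio of 0.7. This figure is for EDSS; none is given for the mRS.

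**2. Inputs.** From the documents: 525 per arm less 20% lost by month 36 gives 420 per arm, and "All statistical tests will use a two-sided p value of 0.05 unless otherwise specified". Assumed, because the documents are silent: the distribution of mRS change, progression meaning at least one grade worse, and the treatment effect.

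**3. Formulas.** Treated risk p₂ = 1 − (1 − p₁)^0.7. Binary variance of the log odds ratio: 1/(n p₁(1−p₁)) + 1/(n p₂(1−p₂)). Ordinal variance (Whitehead): 12 / (N(1 − Σp̄³)), with N = 840 and p̄ the mean category probability over arms. Power = Φ(|ln OR|/SE − 1.960).

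**4. One case in full.** Placebo improved / same / +1 / +2 = 10/50/32/8%.
- p₁ = 0.40, p₂ = 1 − 0.6^0.7 = 0.3006, OR = 0.645, ln OR = −0.439.
- Binary: variance 0.0212, SE 0.146, power Φ(3.01 − 1.96) = 85.3%.
- Ordinal: the same odds ratio at every cut gives 14.7/55.2/24.8/5.3% on treatment; Σp̄³ = 0.171; variance 12/(840 × 0.829) = 0.0172; SE 0.131; power Φ(3.34 − 1.96) = 91.7%.

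**5. Range under a common odds ratio, hazard ratio 0.7, 420 per arm.**

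| Placebo change (improved/same/+1/+2, %) | Binary | Ordinal | Gain (points) |
|---|---|---|---|
| 10/50/32/8 | 85.3% | 91.7% | 6.4 |
| 10/65/22/3 | 66.0% | 80.3% | 14.3 |
| 5/70/22/3 | 66.0% | 75.1% | 9.1 |
| 5/80/13/2 | 44.8% | 58.7% | 13.9 |
| 2/58/38/2 | 85.3% | 87.6% | 2.3 |

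If only 0 or +1 can occur, the two tests coincide and the gain is 0. Reading 30% as a risk ratio instead (40% to 28%), binary power is already 95.8% and the gain is 0 to 3 points. With 15/60/20/5 and a risk ratio of 0.7 the gain is 14.8 points; with an odds ratio of 0.75 and 525 per arm it is 16.0. The upper end is soft: in a simulation of steady latent drift with treatment slowing or halting it by 35% (36 settings, tests stratified by baseline mRS), gains ran from 0.2 to 17 points.

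**6. When the sign reverses.** Suppose treatment multiplies the risk of worsening by 0.7 and leaves the proportion improved untouched. A tie-corrected Wilcoxon test then has 75.9% power against 85.0% binary (5/65/27/3) and 85.5% against 95.8% (10/50/32/8). Losses reach about 30 points for a wide six-category spread.

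The reversal does not need improvement to be exactly unaffected. Take 10/50/32/8 with worsening cut to 30.1%, and approximate rank-test power by Φ{(|θ − ½| − 1.96√V₀)/√V₁}. Here θ is the probability of a worse grade on treatment plus half the ties, V₀ = (1 − Σp̄³)/(6n), and V₁ is the unpooled variance. With improvement on treatment at 12.3%, θ = 0.447, √V₀ = 0.0180 and power is 84%. With improvement at 10.0%, 11.2%, 13.5% and 14.7%, power is 70%, 79%, 88% and 92%. Against 85% for the binary test, break-even lies at about half the shift in improvement that a common odds ratio implies (10.0% to 14.7%).

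**The case against.** The strongest reply is that nothing here is an error. A pre-specified logistic regression on the proportion progressing is valid, matches how the EDSS is handled, and suits a trial whose aim is to slow worsening. All of that stands. The EDSS parallel is fair, although the EDSS endpoint has a stated regulatory basis and the mRS endpoint has none.

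Second, the gain depends on assumptions, and a treatment that only prevents worsening favours the binary test. This also stands, and is why the binary result should be kept. A slowing effect does not by itself imply that case: in the drift simulations, slower drift also raised observed improvement, because more participants could still be graded lower (8.1% to 10.6% in one setting).

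Third, the signed-off SAP is not shown and may hold an ordinal analysis or the definition of mRS progression. That is possible, and the missing definition is no criticism. The point rests on the analysis the article does state.

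A reader might infer more than this. One stronger reading is that the cut typically costs 5 to 15 points of power; the documents give no mRS distribution, rate or effect, and the assumed cases run from nothing upwards and can change sign. Another is that the direction of change is lost; it is not, since worse is still separated from not worse. A third is that the primary result is weakened; it does not use the mRS.

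**Conclusion.** The point holds as a matter of efficiency for one secondary outcome. The article fixes a binary mRS endpoint, without baseline mRS in the model and without a stated reason, and describes no analysis of the ordered grades. Type I error and the primary analysis are not in question.

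The loss is roughly 0 to 16 points of power, assuming about 420 per arm (the 16 itself arises at 525), a common odds ratio across grades, progression meaning at least one grade, and the change distributions shown. It is largest where a fair share of participants improve and worsening is not very common, and nil where only one-grade worsening occurs. It becomes a gain for the binary test if treatment cuts worsening and leaves observed improvement unchanged or nearly so. This is a worthwhile refinement rather than a necessary correction.

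**What to change.** In Analyses, Secondary outcomes, pre-specify a proportional-odds regression of the month-36 mRS grade with treatment, baseline mRS and the minimisation variables, reporting the common odds ratio with 95% CI. Baseline mRS is needed so that the comparison reflects change. Keep the proportion with mRS progression alongside it, adding baseline mRS to that logistic model too. State in advance which result carries the mRS conclusion, and report both.

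The cost is one extra model on data already collected, plus a dated amendment to the signed-off SAP, made before anyone deciding on it has seen mRS results by arm. The ordinal model assumes a similar odds ratio across grades, is slightly harder to explain, and may have lower power in the worsening-only case. The retained binary result covers that case.

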### Compliance

Participants will be considered to be compliant with their randomised intervention if the summary measure of compliance is over 90%, which means they took 80 mg/2 tablets on at least 90% of days over the first 36 months of follow-up, or until the date of confirmed progression, death or withdrawal if these happened before 36 months. A secondary measure of compliance will consider participants compliant if they took either high (80 mg/2 tablets) or low (40 mg/1 tablet) dose on at least 90% of days.

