## Intervention

### Form

Oral Sandoz simvastatin 40 mg film-coated tablets or matching placebo.

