### Dosage

Participants will receive either simvastatin 80 mg (initially 40 mg at randomisation, then escalated after 1 month) or the same quantity of placebo (of the same colour/size), taken once daily at night.

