### Outcomes

#### Primary outcome

The primary outcome will evaluate the effect of daily use of simvastatin (80 mg) versus placebo on disability progression at 6-monthly intervals in patients with SPMS, based on change in EDSS score compared with baseline. Progression of disability will be defined as an increase of at least 1 point if the baseline EDSS score <6, or an increase of 0.5 point if EDSS score ≥6. The initial disability progression event is finalised as positive if the disability is sustained and confirmed ≥6 months later. This allows for disability confirmation to take place if a visit is missed. This is termed CDP. The date of progression (if confirmed) will be the initial date of the progression event. EDSS is generally assessed in person, but there will be capacity for this to be collected remotely via the telephone.^46^ Time to first CDP will be compared between the simvastatin and placebo arms over treatment of up to 54 months. EDSS assessment will be performed by a blinded assessor, in line with the current version of the neurostatus scoring guidance (v04/10.2)

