## Analyses

### Statistical analysis

The primary statistical analysis will be based on all participants as randomised, irrespective of subsequent compliance with allocated treatment (intention-to-treat analysis). A secondary per-protocol analysis will be carried out including only participants who were able to comply (see the ‘Compliance’ section) with simvastatin or placebo treatment.

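### The main compliance measure scores the planned 40 mg first month as non-compliance, so entry to the per-protocol set depends on how early a participant progresses

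*Protocol article*

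**What the plan says.** All places are in the protocol article.

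- **Compliance.** The summary measure is met if "they took 80 mg/2 tablets on at least 90% of days over the first 36 months of follow-up". For some participants the counting window is shorter and runs only "until the date of confirmed progression, death or withdrawal if these happened before 36 months". A secondary measure also accepts days on the low dose (40 mg, one tablet).
- **Form and Dosage.** The product is "Oral Sandoz simvastatin 40 mg film-coated tablets or matching placebo". The 80 mg dose is reached in steps: "initially 40 mg at randomisation, then escalated after 1 month". Month 1 is therefore one tablet a day in both arms.
- **Primary outcome.** "The date of progression (if confirmed) will be the initial date of the progression event". Confirmation comes at least 6 months later.
- **Trial schedule.** After the 1-month clinic visit and the 3-month telephone check there are "further assessment visits at 6-monthly intervals from 6 months postrandomisation onward", so month 6 is the first scheduled EDSS assessment after baseline.
- **Statistical analysis.** "A secondary per-protocol analysis will be carried out including only participants who were able to comply", with a pointer to the Compliance section. The primary analysis is intention-to-treat.
- **Health economics analysis.** The secondary within-trial analysis is also per-protocol, in line with the main statistical analysis.

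**The concern.** The numerator counts only two-tablet days. The denominator appears to start with follow-up, that is, at randomisation. A participant who follows the titration exactly is charged a full month of non-compliance, while one who took two tablets from day 1, against the schedule, would score 100%.

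Over a 36-month window that month costs little. Over a short window it decides the result, and the window is shortened by the primary endpoint itself. Membership of the per-protocol set then depends on the outcome being analysed: people who did everything asked of them can be left out because they progressed early. The analysis would no longer describe participants who complied with their allocated treatment, and it would lose events from the start of follow-up.

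**Working it through.** **Inputs.** Compliance threshold 90% (Compliance). One month at one tablet (Dosage). First assessment at month 6 (Trial schedule). From Power and sample size: 525 per arm, 330 events, 90% power, 30% relative reduction (taken as HR 0.70), 8% progression per 6 months (taken as the placebo rate) and 20% loss by 36 months. The two-sided 5% level is in Analysis plan.

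**The plan's own figures first.** Schoenfeld's formula gives 4 × (1.960 + 1.282)² / (ln 0.70)² = 330.4 events, which agrees with the stated 330. The 8% rate gives 1 − 0.92⁶ = 39.4% by 36 months, which agrees with the stated 40%.

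**Ceiling with perfect adherence**, (T − 1)/T:

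| Window closes at month | Ceiling | Missed days still allowed |
|---|---|---|
| 6 | 83.3% | none; already about 12 days short |
| 12 | 91.7% | about 6 |
| 18 | 94.4% | about 24 |
| 24 | 95.8% | about 43 |
| 36 | 97.2% | about 79 |

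The ceiling equals 90% when (T − 1)/T = 0.9, so T = 10 months. If the titration step lasts 28 or 35 days, the break-even moves to 9.2 or 11.5 months. The month-6 ceiling is then 84.7% or 80.8%, below 90% either way.

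**Adherence needed after escalation**, 0.9T/(T − 1): at T = 12 it is 10.8/11 = 98.2%; at T = 36 it is 32.4/35 = 92.6%.

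**Which date closes the window.**
- *Onset.* The window of a month-6 progressor closes at T = 6. Failure is certain.
- *Confirmation.* The same person's window closes at T = 12 at the earliest. Failure is not certain, but only about 6 missed days in the year are tolerated.

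**People concerned on the onset reading, before loss to follow-up.**
- Placebo: 525 × 0.08 = 42.
- Simvastatin: 525 × (1 − 0.92^0.7) = 525 × 0.0567 = 29.8, about 30.
- Onsets by month 36: 525 × (0.3936 + 0.2955) = 361.8, where 0.2955 = 1 − 0.92^(6 × 0.7).
- Share: 71.8/361.8 = 19.8%.

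Against the 330 planned events, 71.8 is about 22%. As a gauge of lost information only, Schoenfeld power at HR 0.70 falls from 90% with 330 events to about 82% with 258.

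**Effect on the hazard ratio.** Expected event counts were put through a Cox model to month 36, with all month-6 onsets removed.
- Constant HR 0.70: the HR is 0.70 before and after removal.
- Assumed delayed effect (HR 1.0 in the first 6 months, 0.65 after): intention-to-treat gives about 0.72 (0.725 with the plan's 20% loss) and the reduced set gives 0.65. This pattern is an illustration; the plan does not assume it.

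**The case against.** Four objections carry weight.

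1. **The closing date is open to reading.** The Compliance section speaks of the date of confirmed progression. The Primary outcome section dates progression, if confirmed, at onset, which is not quite the same phrase, and the censoring rule for the primary analysis uses confirmed progression for something that occurs at a visit. This stands. A reader might infer that every month-6 progressor is automatically excluded. That follows on the onset reading, which the dating rule favours, but not on the confirmation reading.

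2. **The secondary measure already counts 40 mg days.** Under it, a fully adherent month-6 progressor scores 100%. This stands in part. The pointer from the per-protocol analysis is to a section that holds both measures, but nothing names the secondary one as the criterion. It also accepts participants who stay on a reduced dose for the long term, which the dose modification rules allow, so it answers a different question.

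3. **A flattered per-protocol hazard ratio is not shown.** This stands. A reader might infer that the rule makes the drug look better. Under the plan's constant 30% reduction the cost is events and precision; the estimate moves only if the effect is non-proportional. Nor do people who die or withdraw before month 10 add to the loss of events. They fail the rule too, but onset is first assessed at month 6 and confirmed at month 12 or later, so none of them can have a confirmed event.

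4. **The signed-off analysis plan is not shown and may define the window differently.** That is possible. The point, however, concerns a rule the article states outright, which conflicts with its own titration step. If the analysis plan differs, the two need to be reconciled.

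**Conclusion.** The point holds, at moderate severity. The stated compliance rule conflicts with the planned titration and ties the attainable score to the date of progression, death or withdrawal. On the onset reading, about 72 fully or partly adherent participants (42 placebo, 30 simvastatin) fail whatever they do. On the confirmation reading nobody with a confirmed event is certain to fail, but the tolerance for missed days still runs from about 6 at month 12 to about 79 at month 36.

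The counts rest on 8% per 6 months being the placebo rate, a constant HR of 0.70, a one-month titration and no loss to follow-up. The rule is the same in both arms; the counts differ only because the assumed effect gives fewer early events on simvastatin.

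The primary intention-to-treat analysis, its 330-event target and its power are untouched, and so is the primary health-economic analysis. A reader might take this as a threat to the trial's main conclusion; the documents do not support that. What is at stake is whether the secondary per-protocol analyses, clinical and economic, describe compliers.

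**What to change.** In the Compliance section, and in the analysis plan if it carries the same rule:

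1. Score each day against the dose due on that day under the planned titration, so that one tablet in month 1 counts as compliant. Alternatively, start both numerator and denominator at the 1-month escalation visit. Either way a fully adherent participant with onset at month 6 scores 100% rather than 83.3%. Tying the score to the planned titration, and not to later individual dose changes, keeps the main measure distinct from the secondary one.
2. State whether onset or confirmation closes the window.
3. State which of the two measures defines the per-protocol set, and use the same set for the clinical and the health-economic analyses.
4. Settle the threshold wording: the section says both over 90% and at least 90%.

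The cost is a few sentences and the re-derivation of one variable, before the analysis is unblinded. No new data are needed, and neither the dose nor the visit schedule changes.

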### Dose modification and stopping

The dose may be varied for patients experiencing hepatic effects, myopathy/rhabdomyolysis or other adverse events at the principal investigator’s discretion. Where elevated alanine aminotransferase (ALT), aspartate aminotransferase (AST) or creatine kinase (CK) levels are sustained at ≥3×upper limit of normal (ULN), it is recommended that the dose is lowered (from 80 mg (active/placebo) to 40 mg (active/placebo)), with rechallenge at the higher dose possible after parameters return to normal. For ALT, AST or CK levels ≥5×ULN, trial medication should be stopped, with rechallenge only permissible where the intervention was clearly determined to be non-causally related (eg, another intercurrent medication or infection, which has now resolved, produced the biochemical abnormalities).

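### Compliance is scored only up to progression, so per-protocol membership depends on the outcome, and the per-protocol hazard ratio is biased when stopping is spread over follow-up and differs between arms

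*Protocol article*

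**What the plan says.** Under Statistical analysis, the primary analysis is intention-to-treat, and "A secondary per-protocol analysis will be carried out including only participants who were able to comply" with their allocated treatment, as defined under Compliance. That section asks for 80 mg (two tablets) "on at least 90% of days over the first 36 months of follow-up, or until the date of confirmed progression, death or withdrawal" if one of these came before 36 months. A secondary measure accepts one or two tablets with the same 90% threshold.

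Four other statements bear on this:

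- **Duration:** participants who stop tablets stay in follow-up unless they withdraw consent.
- **Dosage:** everyone takes 40 mg for the first month. The Compliance section does not say whether that month counts as compliant under the 80 mg measure.
- **Primary outcome:** a confirmed progression is dated at the initial event, so the progression date that closes the compliance window could be the initial or the confirming visit.
- **Dose modification and stopping:** at liver enzyme or creatine kinase levels of at least five times the upper limit of normal, "trial medication should be stopped". At sustained levels of at least three times the limit, a lower dose is recommended, and days on that dose fail the 80 mg measure.

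**The concern.** A per-protocol set should not be selected on the event that it is used to analyse. Here the number of compliant days required depends on when, or whether, the participant progresses. A non-progressor who stops at month 24 scores 24/36 = 67% and is removed together with 24 compliant, event-free months. A participant who progressed at month 12, and would also have stopped at month 24, scores 100% on the any-dose measure and is kept as an event.

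If both arms lose participants in the same way, the distortion cancels in the HR. If one arm stops more, it loses more event-free time and looks worse. The stopping rule gives a plausible route to such a difference. The per-protocol result is the only efficacy estimate under compliance that the article describes, and the Health economics analysis section also plans a per-protocol secondary analysis. A reader who saw 0.76 per protocol beside 0.71 by intention to treat could wrongly conclude that taking the drug as directed helps less.

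**Working it through.** **Design figure.** The article plans "90% power to demonstrate a 30% relative reduction in disability progression for simvastatin versus placebo", "at the conventional 5% significance level" (two-sided, per Analysis plan), with 1:1 allocation. Schoenfeld's formula gives 4(1.960 + 1.282)² / (ln 0.70)² = 42.03 / 0.1272 = 330.4, or 331 rounded up, against the stated 330. An HR of 0.70 is therefore a fair reading of the design effect. The article gives no figure for stopping or for per-protocol bias.

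**Inputs from Power and sample size.** Placebo progression is 8% per 6 months (1 − 0.92⁶ = 39%, against 40% stated by 36 months), and loss is 20% by 36 months.

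**Assumptions not in the article.** Stopping is permanent, unrelated to prognosis and at a constant rate. Drug effect does not fade after stopping, which isolates the selection effect.

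**Step 1: who qualifies, with the first month credited.** If a proportion p stops by 36 months, the chance of reaching 90% over a window of W months is (1 − p)^(0.9W/36).

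| p | W = 6 | W = 12 | W = 36 |
|---|---|---|---|
| 15% | 98% | 95% | 86% |
| 20% | 97% | 94% | 82% |
| 30% | 95% | 90% | 73% |

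The gap between a 6-month and a 36-month window is about 11 points at 15% stopping (97.6% − 86.4%) and 22 points at 30% (94.8% − 72.5%). Equal gaps cancel between arms; unequal gaps do not.

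**Step 2: effect on the HR.** This comes from simulation with 400,000 participants per scenario. Ranges cover the two readings of the progression date.

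| Stopping by 36 months, simvastatin v placebo | Per-protocol HR, true HR 1 | Per-protocol HR, true HR 0.70 (ITT 0.71) |
|---|---|---|
| 20% v 20% | 1.00 | 0.71 |
| 25% v 15% | 1.03–1.04 | 0.73–0.75 |
| 30% v 15% | 1.05–1.07 | 0.75–0.76 |
| 40% v 20% | 1.07–1.11 | 0.77–0.79 |

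The simulated intention-to-treat (ITT) value is 0.71 rather than 0.70 because events are grouped at visits.

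**Step 3: early stopping.** If all stopping falls in the first 12 months (30% v 15%) and the window runs to the confirming visit, the per-protocol HR is 1.00 at true HR 1 and 0.71 at true HR 0.70. Across the variants run, the shift was about 0% to 4%.

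**Step 4: first month counted as non-compliant.** That month uses 1/6 = 16.7% of a 6-month window, 1/12 = 8.3% of a 12-month window and 1/36 = 2.8% of a 36-month window.

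- If the initial date closes the window, nobody who progresses at month 6 can reach 90%.
- If the confirming visit closes it at month 12, such a participant may miss about 36.5 − 30.4 = 6 further days. A participant followed for 36 months may miss about 109.6 − 30.4 = 79.
- On that second reading, with an assumed mean of 3% sporadic missed days and 20% stopping, 42% of month-6 progressors qualify against 74% of fully followed non-progressors. The direction of selection reverses.
- The HR at true HR 1 with 30% v 15% stopping is still 1.04–1.05.

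**Step 5: windows that ignore progression.** With 30% v 15% stopping, scoring the first 6 months for everyone gives 1.00 at true HR 1 and 0.71 at true HR 0.70.

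**The case against.** Ending the window at the event has a rationale: dosing after progression cannot affect that event, and scoring everyone to 36 months would penalise people who stop because they progressed. This stands as a reason not to score past the event. It does not justify deciding membership of the whole set on a window that the outcome closes.

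The size rests on assumed rates. The article gives neither the frequency nor the timing of stopping, and its only tolerability statement is that simvastatin was safe and well tolerated in phase 2. The shift is also small beside sampling error. With 330 events the standard error of the log HR is about 2/√330 = 0.11, so 1.04 and 1.06 are ln 1.04/0.11 = 0.36 and ln 1.06/0.11 = 0.53 standard errors from 1. If simvastatin is the arm stopped more, the bias is conservative. All of this stands and limits the weight of the point. It does not remove a systematic error, which a larger sample would not cure.

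A signed-off analysis plan exists and is not shown. It may settle how the first month is counted and which date closes the window. The article nevertheless states the membership rule itself, and the flaw lies in that rule.

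Two stronger readings are tempting. One is that early progressors always qualify more easily. That holds under the any-dose measure or with the first month credited, but the 80 mg measure read literally reverses it. The other is that any arm difference in stopping biases the HR. Step 3 shows that a 15-point difference confined to the first year has little or no effect.

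**Conclusion.** The point holds in a conditional form. The stated rule makes per-protocol membership depend on the primary event. When stopping is spread over follow-up and differs between arms, the per-protocol HR is biased against the arm that stops more, even if stopping is unrelated to prognosis. Under the assumed 25% to 30% v 15%, the shift is roughly 4% to 6% at a true HR of 1, and from 0.71 to about 0.74 to 0.76 at the design effect.

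A reader might infer that a drug with no effect would appear harmful. The documents do not support that: they give no stopping rates, and an HR of 1.04 to 1.06 lies well within sampling error. Nor is the trial's main conclusion at risk, because the primary analysis includes everyone as randomised. This is a systematic but modest flaw in a named secondary analysis, and it is cheap to correct. Separately, the Dosage, Primary outcome and Compliance sections need reconciling on the first month and the closing date, because these decide which participants qualify.

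**What to change.** Enter all randomised participants in the per-protocol Cox model. Censor each at the first scheduled 6-monthly visit at which cumulative compliance since randomisation is below 90%. For this analysis, count the planned first month at the allocated tablet number as compliant. Both details matter: without the credit, compliance under the 80 mg measure is 0% throughout month 1, and with daily checking one missed dose in the first nine days would censor an otherwise adherent participant. Checked at visits with the first month credited, the rule returned the intention-to-treat value in every scenario run, including those with sporadic missed doses.

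Use the same rule for the any-dose measure. As a sensitivity analysis, add inverse-probability-of-censoring weights based on the minimisation factors, baseline EDSS and last observed EDSS, since real stopping may be related to prognosis. Report the whole-period compliance score descriptively. State whether the initial or the confirming visit closes that score.

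The cost is a change to the analysis plan and some extra programming. The rule needs compliance dated by visit, which the article does not confirm is collected. If it is not, use a compliance window that does not depend on progression, such as the first 6 months for everyone.
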